**Initial collection**

The Assurance Maladie will be responsible for extracting the data specific to the research and for building up the database.

The data collected will be data characterising GPs: age group (in 5-year increments from the age of 25), sex, classification of the commune of practice (according to INSEE urban area zoning, "major centres" (codes 111, 112, 120), "small centres" (codes 211, 212, 221, 222), "isolated towns" (code 400), and "other communes" (code 300) [46]), activity in terms of number of annual consultations, number of patients in the GP patient base, mode of practice (alone, in a group).

The Assurance Maladie randomises the GPs' places of practice and adds the allocated randomisation arm to the list of participating GPs, according to their place of practice.

The Assurance Maladie extracts data on antibiotic therapy prescriptions from all GPs included in the study (data for the 12 months preceding the visit) for descriptive purposes (T0).

**A 2nd round of** data **collection** will take place at the end of 12 months' follow-up: the French National Health Insurance will extract data on the dispensing of antibiotics prescribed by all GPs included in the study.

The data collection period will begin on the day of the DAM's visit.

- - 1. ***PARTICIPANT IDENTIFICATION***

The data will be centralised by the Assurance Maladie. No nominative data will be exported outside the databases of the Sickness Insurance departments.

The variables were selected after a pilot study, and the health insurance authorities paid close attention to CNIL regulations, to ensure that no data was directly identifiable (which is why the ages of practitioners are grouped into 5-year classes, and the communes classified by type).

- 1. ***Statistics***
     1. ***DESCRIPTION OF PLANNED STATISTICAL METHODS, INCLUDING TIMETABLE FOR INTERIM ANALYSES***

The analyses will be carried out using R 3.6.0 software.

The data will be described by the numbers and percentages of each modality for the qualitative variables and by the minimum, maximum, quartile, mean and standard deviation for the quantitative variables, overall and according to the 3 randomisation arms.

A hierarchical procedure will be used to successively test the comparison between the 3 arms, while maintaining a 5% alpha risk. The first hypothesis tested will be the difference between arm 1 and arm 3. If the test is significant, a second test will be performed comparing arm 1 to arm 2.

- - - 1. *Primary endpoint*

The overall volume of systemic antibiotics dispensed in DDD at the end of 12 months of follow-up, per participating doctor, will be calculated and compared between arms using a Student's t test.

- - - 1. *Secondary endpoints*

In addition to the primary endpoint (assessing the overall volume of systemic antibiotics dispensed at 12 months follow-up), other endpoints will be studied.

1/ The overall volume of systemic antibiotics dispensed in DDD at the end of 3 months of follow-up, per participating physician, will be calculated and compared between arms using a Student's t test. The monthly change in the overall volume of systemic antibiotics dispensed will also be described between arms.

2/ The volume of broad-spectrum systemic antibiotics most frequently responsible for antibiotic resistance in primary care (3^ème^ generation cephalosporins, fluoroquinolones, amoxicillin/clavulanic acid) dispensed in DDD per participating doctor will be calculated and described monthly and over 12 months of follow-up, and for the latter, compared between arms using a Student's t test.

3/ Sub-group analyses :

. Subgroup 1: The volume of systemic antibiotics dispensed to patients aged over 65 in DDD at the end of 12 months of follow-up, per participating doctor, will be calculated and compared between arms using a Student's t test.

. Subgroup 2: the same analysis will be carried out for patients under 6 years of age, and for these same patients on the broad-spectrum systemic antibiotics most frequently responsible for antibiotic resistance in primary care.

The monthly trends for these two sub-groups will also be described according to the randomisation arms.

The overall monthly volume of systemic antibiotics dispensed in DDDs, and by subgroup, will be described for each of the three groups, and represented graphically.

4/ The characteristics of the physicians (age, sex, type of practice, etc.), which may be associated with the overall prescription of systemic antibiotics, will also be investigated using ANCOVA models, adjusted for the randomisation arm.

5/ The secondary endpoints used for the medico-economic analysis are described in section 9. Medico-economic analysis, and in particular chapters 9.2, 9.3 and 9.4.

. The cost-effectiveness analysis will be conducted on the intention-to-treat (ITT) population, i.e. on all randomised healthcare professionals.

. Details of the resources consumed in each arm (averages and dispersion) and the average costs and efficiency per doctor will be calculated for each arm.

. A table will show the difference between the two groups in terms of costs and effectiveness, and the cost-effectiveness ratio will be calculated.

. As costs are not generally distributed according to a normal distribution, the incremental cost-effectiveness ratio and its confidence interval will be estimated using the non-parametric bootstrap method [49].

Finally, the probability that the use of antibioclic associated with a specific DAM visit is cost-effective compared with *a standard DAM visit* will be calculated for different values of willingness to pay for a reduction in antibiotics.

- - 1. ***STATISTICAL JUSTIFICATION FOR THE NUMBER OF INCLUSIONS***

After preliminary work to explore feasibility with the Assurance Maladie teams, the number of eligible doctors was estimated at 2,400 GPs who saw more than 100 different patients in 2018. The average number of DDDs dispensed per doctor in 2018 was 7,671, with a standard deviation of 5,360. In 2018, the average number of DDDs dispensed per doctor was 7671, with a standard deviation of 5360. Due to cluster randomisation, an inflation factor must be applied to calculate the number of subjects. In a previous study in the Loire Atlantique and Vendée regions [47], the average number of GPs per practice was 1.9. We set an intra-class correlation coefficient of 0.05 [50].

With an alpha risk of 5% and power of 80%, we can then demonstrate a significant difference if we have at least an average difference of 450 DDD per doctor (over the 12 months following the DAM visit) between the arms being compared.

- 1. ***Expected degree of statistical significance***

The alpha risk is set at 5%.

- 1. ***Method for taking into account missing, unused or invalid data***

All analyses will be performed on an intention-to-treat (ITT) basis.

The volumes of systemic antibiotics dispensed attributed to doctors who ceased their activity (end of career, moving outside the region, death, etc.) during the study follow-up period will be replaced by multiple imputation. A sensitivity analysis of the per-protocol population will also be carried out, excluding these doctors, as well as those who did not receive a visit from the DAM, and those who were not computerised.

For doctors who have not been visited by the DAMs, the start date of the data collection period will be allocated by drawing lots, and staggered over the 3 months (start date based on the visit dates available for the 3 randomisation arms).

- 1. ***Randomisation***

The Assurance Maladie will generate a list of GP practices that meet the inclusion criteria. It will then randomise the GP practices on a 1:1:1 basis. Doctors will be assigned to the randomisation arm to which their practice has been allocated.

1. **SAFETY / UNDESIRABLE EFFECT**

In the regulatory sense and within the meaning of the Jardé Law, this study does not constitute research involving human subjects. In the regulatory sense and within the meaning of the Jardé Law, this protocol does not involve any change in the usual management of patients, so any adverse events or effects observed will be unrelated to the study.

1. **MEDICO-ECONOMIC STUDY**

This section presents the objectives and methodology of the efficiency analysis, based on a cost-effectiveness analysis. The economic evaluation methodology follows the 2011 recommendations of the French National Authority for Health [49].

- 1. ***Objective, perspective and time horizon of the cost-effectiveness analysis***

The study involves a cost-effectiveness analysis comparing the delivery of antibiotics over a 12-month period in current practice, compared with two alternative strategies

i) an intervention carried out by the Délégués d'Assurance Maladie (Health Insurance Representatives) in general practices, combining a regular visit (with awareness-raising on antibiotic resistance, work on preconceived ideas, feedback on practices) and a demonstration of the use of Antibioclic,

1. an intervention carried out in the same way by the Délégués d'Assurance Maladie, but without Antibioclic being demonstrated.

This analysis will be carried out from the point of view of the Assurance Maladie Obligatoire over a 12-month period.

Costs will be estimated on the basis of information retrieved from the SNDS databases extracted by the Assurance Maladie in Pays de la Loire. The resources consumed will be valued at Assurance Maladie prices for drugs.

Given that two strategies will be compared with current practice, it may be necessary to estimate several incremental cost-effectiveness ratios (ICERs). A dominance analysis will be carried out to check whether certain interventions are dominated, i.e. more costly and less effective than another intervention. The average incremental cost-effectiveness ratio will be presented, together with its 95% confidence interval.

Univariate and multivariate sensitivity analyses will be carried out to check the robustness of the results to changes in assumptions about certain study parameters.

- 1. ***HEALTHCARE CONSUMPTION AND VALUATION***

The costs of the three strategies compared will be estimated in three stages [48]:

. collection of resources consumed,

. the unit monetary value of resources,

. estimated total costs.

Deliveries and costs of systemic antibiotics will be estimated using information retrieved from SNDS databases extracted by the Assurance Maladie in Pays de la Loire. The resources consumed will be valued at Assurance Maladie prices for drugs.

The resources used as part of the study will include :

. the costs associated with preparing and holding the training course,

. training time for DAMs,

. the development of communication material,

- the time it takes to create a digital visual aid,

- time for role-playing,

- the time it takes to write a sales pitch,

- time to rewrite the memo cards.

. time doctors

. the average duration of use of Antibioclic by doctors

We will take into account antibiotic dispensing based on the doctor's prescription and the monitoring of activity over a 12-month period. The costs will be calculated using Assurance Maladie tariffs.

This will be done by combining the results of the two previous stages. Given the 12-month time horizon, the costs will not be discounted. We will present the average costs per patient in each arm.

- 1. ***Efficiency data***

Effectiveness will be measured by the ratio between deliveries of defined daily doses (DDD) observed in the Assurance Maladie databases and the WHO defined daily doses between the different scenarios in the analysis [46-47].

We will look at defined daily doses (DDD) of all types of systemic antibiotics for all patients per 100 consultations [51]. To do this, we will stratify by specific antibiotic types (ie, tetracyclines, quinolones, β. lactamine/penicillin, other β. lactamine, other antibacterials, unspecified, etc.).

Finally, we will stratify the patient populations into 4 classes: young children (0 to 6 years), children over 6 years and adolescents (7 to 17 years), young adults (18 to 65 years) and finally the elderly (over 65 years) and between men and women.

- 1. ***Presentation of results***

In accordance with ISPOR recommendations on economic evaluation [52,53], we will present the results of the medico-economic analysis as follows:

. average antibiotic costs per arm and the difference in costs with its 95% confidence interval

. Mean efficacy per arm and the difference in efficacy with its 95% confidence interval

As costs are not generally distributed according to a normal distribution, the incremental cost-effectiveness ratio and its 95% confidence interval will be estimated using the non-parametric bootstrap technique.

Finally, sensitivity analyses will be carried out to study the robustness of the results on certain key parameters of the study.

1. **ADMINISTRATIVE AND REGULATORY ASPECTS**
   1. ***Right of access to source data and documents***

The data extracted as part of the study will not be nominative, whether it concerns physician data or patient data. They will only be transmitted to the sponsor or any person duly authorised by the sponsor, and, where applicable, to the authorised health authorities, under conditions which guarantee their confidentiality (see 7.1.COLLECTION AND PROCESSING OF STUDY DATA).

There is no provision for access to source documents. This means that there will be no export of nominative data outside the usual health insurance databases.

The data collected during the trial will be processed electronically, in compliance with CNIL requirements.

- 1. ***Computerised data and submission to the CNIL***

Data processing will be recorded in the Nantes University Hospital's RGPD register.

The data collected during the study will be kept in a computer file that complies with the amended French Data Protection Act of 6 January 1978, Law No. 2018-493 of 20 June 2018 on the protection of personal data and Regulation (EU) 2016/679 of the European Parliament and of the Council of 27 April 2016 on the protection of individuals with regard to the processing of personal data and on the free movement of such data (RGPD).

The protocol falls within the scope of the MR004 Reference Methodology to which Nantes University Hospital complies.

- 1. ***Inspection / Audit***

This study may be subject to inspection or audit. The sponsor and/or the investigators must be able to give the inspectors or auditors access to the data.

- 1. ***Ethical considerations***
     1. **Procedures for obtaining consent**

**This is a study outside the scope of the Jardé Law** [54,55]. Research involving the human person does not include *research aimed at evaluating the methods used by healthcare professionals or teaching practices in the healthcare field.*

*In addition, the study provides for an exemption from the requirement to inform patients by reference to international standards as defined by the IRB in the light of the following criteria:*

*"(1) the research is designed to evaluate possible changes in public health programs, and (2) the research can not practicably be carried out without the waiver". [56]*

- - 1. **Ethics Committee**

The experimental protocol will be analysed in accordance with regulatory ethical imperatives. This is a study outside the scope of the Jardé Law. The project will be subject to the prior opinion of an Ethics Committee that rules on non-RIPH projects, such as that of the Collège National des Généralistes Enseignants (CNGE).

- 1. ***Amendments to the protocol***

Substantial changes must be set out in an updated dated version of the protocol.

- 1. ***Publication rules***

Authors will be determined on the basis of their contribution to the study. The coordinating investigator will draw up the list of authors.

Any publication resulting from this research will carry the mention: "This study was supported by a grant from the French Ministry of Health (PREPS 2019)".

1. **PROJECT COORDINATION ARRANGEMENTS**

The project was co-constructed with the Pays de la Loire health insurance scheme.

- 1. ***Role of each team***
- **Department of General Medicine, University of Nantes**

. Coordinates the study

. Responsible for the scientific development of the study: review of the international scientific literature, design, methodology, etc.

. Co-responsiblefor developing the intervention

. Co-responsible for organising training meetings and presentations to health insurance delegates

. Responsible for statistical data analysis

. Responsible for the scientific promotion plan

- **Department of Infectious and Tropical Diseases, Nantes University Hospital**

. Participates in the coordination of the study

. Providing scientific expertise in infectiology and antibiotic resistance

. Participate in the scientific development of the study: international scientific literature, design, methodology, etc.

. Co-responsible for developing the intervention

. Co-responsible for organising training meetings and presentations to Health Insurance delegates

. Participate in the interpretation of results and in the scientific development plan

- **Health insurance**

. Co-responsible for coordinating the study

. Responsible for the inclusion of participating GPs

. Co-responsible for organising training meetings and presentations to the Health Insurance Representatives

. Responsible for coordinating the DAM network

. Responsible for randomisation

. Responsible for extracting and collecting data from the SNDS.

- **MEDQUAL**

. Expertise in infectiology and antibiotic resistance

. Expertise on training needs in infectiology and antibiotic resistance.

- **ANTIBIOCLIC**

. Expertise in infectiology and antibiotic resistance

. Design of the Antibioclic tool (made available to GPs as part of the intervention)

. Expertise on the needs and practices of general practitioners .

- 1. ***Steering Committee***

All the teams take part in the steering committee. This committee defines the general organisation and progress of the project, coordinates information and decides what to do in unforeseen circumstances.

*References*

2. de Kraker ME, Stewardson AJ, Harbarth S. Will 10 million people die a year due to antimicrobial resistance by 2050? PLoS Med. 2016;13:e1002184.
4. Centers for Disease Control and Prevention (CDC). Vital signs: carbapenem-resistant Enterobacteriaceae. MMWR Morb Mortal Wkly Rep 2013;62:165-70.

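### Each GP's pre-visit antibiotic volume is collected but kept out of the primary comparison, giving up precision by an amount that depends on a pre/post correlation the protocol does not state

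*Protocol*

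**What the plan says.** Under Initial collection, the health insurer "extracts data on antibiotic therapy prescriptions from all GPs included in the study (data for the 12 months preceding the visit) for descriptive purposes". No other analysis use of these data is given.

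The Primary endpoint paragraph says that the 12-month volume of systemic antibiotics, "per participating doctor, will be calculated and compared between arms using a Student's t test". No covariate is named. The Secondary endpoints paragraphs give the same test to the 3-month volume, the 12-month broad-spectrum volume, and the volumes for patients over 65 and under 6.

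The one model with covariates is item 4 of the Secondary endpoints: doctor characteristics that may be associated with overall volume "will also be investigated using ANCOVA models, adjusted for the randomisation arm". The factors listed for it under Secondary evaluation criteria are age, sex, type of commune, group or independent practice, number of procedures and number of registered patients. Prior antibiotic volume is not among them.

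The Randomisation section allocates practices 1:1:1 and mentions no stratification. The sample-size paragraph rests on the raw spread between doctors: "The average number of DDDs dispensed per doctor in 2018 was 7,671, with a standard deviation of 5,360". It mentions no baseline adjustment.

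**The concern.** The outcome is a raw yearly total per doctor, and its SD is 70% of its mean (5,360 / 7,671). A GP enters the trial with as few as 100 different patients in the year. Much of the spread is therefore plausibly stable: large and small patient bases, and high and low prescribing habits. A doctor's own volume in the preceding year is the natural measure of that stable part. The protocol plans to collect it for every included doctor and then leaves it out of the test.

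At stake is the trial's ability to detect the effect it names. The testing procedure is hierarchical: arm 1 against arm 2, the question of what the Antibioclic demonstration adds, is tested only if arm 1 against arm 3 is significant. Low power in the first test therefore closes off the second as well. More doctors cannot supply the missing power, because the trial already takes all eligible GPs in the region.

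**Working it through.** **Inputs from the protocol**
- SD 5,360 and mean 7,671 DDD per doctor (2018); 2,400 eligible doctors; 1.9 GPs per practice; intra-class correlation 0.05; alpha 5%; power 80%; stated detectable difference 450 DDD (sample-size paragraph).
- 1:1:1 allocation (Randomisation), hence about 2,400 / 3 = 800 doctors per arm.

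**Assumptions**
- Two-sided test, since the protocol does not give the sidedness.
- The same design effect applies after adjustment.
- The correlation r between pre-visit and follow-up 12-month volume is not in the protocol, so a range is shown.

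**Step 1: the planned, unadjusted comparison**
- Design effect = 1 + (1.9 − 1) × 0.05 = 1.045.
- SE of a difference between two arms = 5,360 × √(2 × 1.045 / 800) = 274 DDD.
- Detectable difference = (1.960 + 0.842) × 274 = 768 DDD, or 10.0% of the mean. The protocol's 450 DDD (5.9% of the mean) is not reproduced. A one-sided test gives 681 DDD, which does not reproduce it either.
- Power at 450 DDD = Φ(450 / 274 − 1.960) = Φ(−0.32), about 38%.
- Doctors needed per arm for 450 DDD = 2 × (1.960 + 0.842)² × (5,360 / 450)² × 1.045, about 2,328. The region has about 2,400 in all.

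**Step 2: adjustment for the doctor's own pre-visit volume**

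The residual SD is 5,360 × √(1 − r²). The share of variance removed is r². The rest follows as in step 1.

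| Assumed r | Variance removed | SE (DDD) | Detectable difference (DDD) | Power at 450 DDD |
|---|---|---|---|---|
| 0 (as planned) | 0% | 274 | 768 | 38% |
| 0.5 | 25% | 237 | 665 | 48% |
| 0.7 | 49% | 196 | 548 | 63% |
| 0.8 | 64% | 164 | 461 | 78% |
| 0.81 | 66% | 161 | 450 | 80% |
| 0.9 | 81% | 119 | 335 | 97% |

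**Step 3: thresholds**
- More than half the variance is removed only if r² > 0.5, that is r > 0.71.
- The SE is halved only if √(1 − r²) < 0.5, that is r > 0.87.
- 450 DDD at 80% power needs r = √(1 − (450 / 768)²), about 0.81.

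**The case against.** The best defence is that leaving out a baseline covariate is an efficiency choice, not an error. Under randomisation the unadjusted difference is unbiased, and chance imbalance in prior volume is already part of the 274 DDD standard error. That is correct. The point is about precision, and nobody should infer that the unadjusted result would be invalid for this reason.

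A second defence is that the analysis model belongs in a statistical analysis plan. It does not answer the point here, because the protocol itself names the test and assigns the baseline data to description.

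Several stronger readings are tempting, and the protocol does not support them:
- **That most of the precision is lost.** No pre/post correlation is given. At r = 0.5 only a quarter of the variance goes.
- **That adjustment is the only free way to reach 450 DDD.** It reaches 450 only from r of about 0.81. Number of consultations and size of the patient base are also collected and could serve as covariates.
- **That adjustment removes baseline imbalance.** It reduces it.
- **That season biases the 3-month comparison.** Visits are staggered over about three months. However, arm 3 visit dates are recorded too, and unvisited doctors receive start dates drawn from the visit dates of all three arms. No timing difference between arms is shown, so season adds noise. The same months a year earlier would reduce that noise but not abolish it, since years differ.
- **That every secondary volume can be adjusted without new data.** The baseline extract is described in terms of prescriptions and the follow-up extract in terms of dispensing. Nothing says that the baseline can be split by month, drug class or patient age.

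A doctor who began practising during the preceding year would also have a partial baseline. That weakens the correlation but is no reason to discard the covariate.

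**Conclusion.** The point holds as a loss of precision on the primary endpoint. The protocol collects the pre-visit volume, confines it to description, and fixes a test that ignores it. Any non-zero r makes adjustment more precise, without introducing bias.

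The size is conditional. Over assumed r from 0.5 to 0.9, the detectable difference falls from 768 to between 665 and 335 DDD, and power at 450 DDD rises from about 38% to between 48% and 97%. A high r is plausible given the wide spread and the low entry threshold, but it remains an assumption.

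A reader might infer that adjustment rescues the sample-size statement. It does not. That 450 DDD fails to follow from the stated inputs is a separate finding and needs its own correction.

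**What to change.** Before outcome data are seen, replace the Student's t test for the primary endpoint with a linear model of 12-month DDD on arm and the doctor's own 12-month pre-visit volume, allowing for clustering by practice. Report the unadjusted difference as a supporting figure. Amend the Initial collection paragraph so that the pre-visit data serve the analysis as well as the description, and state that the baseline is computed in DDD by the same method as the outcome.

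Apply the same model to the broad-spectrum, over-65 and under-6 volumes, each with its own baseline, where the extract can be split by class and age. For the 3-month volume, use the same calendar months of the previous year where a monthly split exists.

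The cost is a few lines of wording. For the primary endpoint the data are already to be extracted. For the secondary endpoints, the Assurance Maladie should first confirm that the baseline extract can be broken down as needed. The 2018 data behind the sample-size figures, together with an adjacent year if available, could be used to estimate r and replace the assumed range.
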